## Methods

### Study setting and subjects

The subjects of this study will be 40 primary care clinics known as 'practices' in a large practice-based research network, the South Texas Ambulatory Research Network. Inclusion criteria for the study are: 1) the practice must have seen at least 60 patients with type 2 diabetes in the past year (in order to insure our sample size of 60 patients per practice); 2) they must be willing and able to use their billing records to identify these patients; and 3) representative members, clinicians, and office staff in the practice must agree to meet with the practice facilitator on a regular basis for one-hour team meetings over 12 months. Exclusion criteria are: 1) multi-specialty practices; 2) practice owned by a large vertically integrated health care system; and 3) practices with five or more physicians.

### Design

This will be a cluster-randomized trial with 20 clinics in the intervention arm and 20 in the control arm. (see Additional File 1) Because the intervention will be implemented in groups of five clinics at three-month intervals, a block randomization to intervention or control groups will be done so that there are four blocks with ten clinics in each block. The randomization scheme will be computer-generated in SPSS 15.0 by the study statistician. Neither the investigators nor the subjects will be blinded. The final chart abstraction for primary and secondary outcomes will be done by a trained abstractor who is blinded to allocation.

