### Data collection

To obtain the dependent and independent variable necessary to accomplish specific aims one through three, clinician and staff surveys will be administered and medical record abstracted in each clinic. Site visits will be conducted in all 40 clinics and will be conducted three times: at baseline after enrollment but prior to randomization, and 12 and 24 months after starting the initial facilitation intervention in each clinic. During each site visit, clinicians and staff will complete surveys to measure the presence of the elements of the CCM as well as communication among clinicians and staff (see description of outcomes below).

The second method of data collection is a blinded medical record abstraction for the primary outcomes: A1c, BP, and lipid levels. This will be accomplished by a trained chart auditor who is blinded to assignment of clinics to intervention or control groups. The abstraction will take place at baseline, after the conclusion of the delayed intervention in the control clinics and 12 months after the end of the intervention in the initial intervention clinics.

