### Sample size and analysis

To test hypotheses for specific aim one, the unit of randomization will be the clinic and the unit of analysis will be the repeated measure of each risk factor for each patient, nested within the clinic. The outcome will be the level of control of each risk factor. We will examine A1c as our primary outcome, with BP and LDL-cholesterol as secondary outcomes. To study change in risk factor level, a hierarchical or random effect model will be used to account for the nesting of repeated measurement of risk factor within patients and patients within clinics [46,47].

The power calculation is derived for the planned cluster randomized design with 20 clinic in each treatment arm and 40 patients each clinic under the hierarchical linear analysis plan (random effects models), and the significance level set at 0.05. For the first specific aim, our primary outcome is A1c and the power estimates are calculated based on the interclass correlation coefficient (ICC) for A1c obtained from a preliminary study of 20 practices [48]. That value is 0.113. For the first specific aim, if the mean decrease in A1c due to intervention is 0.7 or greater, then the power for detecting the intervention effect on A1c is 0.80.

For specific aims two and three, the ACIC score (for specific aim two) and the communication score (for specific aim three) measured repeatedly at the staff and clinician level will be the outcome of primary interest, as it will reflect the presence of elements of the CCM. Due to a similar distributional nature of the ACIC or communication score and risk factors (ACIC and communication scores are measured repeatedly at three time points at the staff level nested within each clinic and are continuous), the three-level random effects model as proposed for specific aim one is appropriate. Sample size and power calculations for these aims are similar to those for the first aim. For the second aim, the ICC of the ACIC score is 0.12 with a standard error of 2.15, resulting in a power of 0.94 to detect a change in ACIC score of at least 1.5 in response to the intervention. For the third specific aim, the ICC for communication scores is 0.33 and the associated standard error is 9.46, thus the power for detecting the intervention effect on communication score is no less than 0.81 if the mean communication score in the intervention group is seven points or greater compared to that for the control group.

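### Clinics are randomised within four calendar blocks, but the stated model has no block term: if fitted as written, the test is unbiased but somewhat conservative, and the control clinics' time zero needs stating

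*Protocol article*

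**What the plan says.** **Randomisation (Design).** The trial is described thus: "This will be a cluster-randomized trial with 20 clinics in the intervention arm and 20 in the control arm". The reason given for blocking is that "the intervention will be implemented in groups of five clinics at three-month intervals", and therefore "a block randomization to intervention or control groups will be done so that there are four blocks with ten clinics in each block". A block is thus a calendar wave. Groups of five intervention clinics in blocks of ten imply 5:5 allocation within each block.

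**Model (Sample size and analysis).** For Aim 1, the stated analysis is this: "random effect model will be used to account for the nesting of repeated measurement of risk factor within patients and patients within clinics". For Aims 2 and 3, "the three-level random effects model as proposed for specific aim one is appropriate". Block appears in neither statement. The text does not say that block is excluded.

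**Timing (Data collection).** "Site visits will be conducted in all 40 clinics and will be conducted three times": once at baseline before randomisation, then "12 and 24 months after starting the initial facilitation intervention in each clinic". The section headed The delayed intervention says that control practices are facilitated only once their time as controls is over.

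**The concern.** When randomisation is restricted within blocks, differences between blocks cancel from the comparison of arms. A model without block does not recognise this. It leaves the block differences in the between-clinic variance, and that variance sets the standard error of the arm effect. The reported uncertainty is then larger than the real one. With only 40 randomised units, the lost sensitivity may matter.

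The blocks also bear on timing. Follow-up visits in all 40 clinics are dated from the start of the initial facilitation, but 20 of those clinics have no initial facilitation. With staggered starts, no single trial-wide date can stand in for it. The wording therefore gives control clinics no date for the 12- and 24-month surveys. The 12-month cut of their dated chart values needs the same index date.

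**Working it through.** **Inputs from the protocol (Sample size and analysis; Design).** k = 20 clinics per arm, m = 40 patients per clinic in the power paragraph (60 elsewhere), ICC = 0.113, effect 0.7, alpha 0.05, stated power 0.80, four blocks of ten clinics.

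**Assumed, because not given.** A two-sided test; the A1c SD; and b, the share of between-clinic variance explained by block.

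**Step 1: the plan's own figure.** In SD² units, the variance of a clinic mean is ICC + (1 − ICC)/m = 0.113 + 0.887/40 = 0.1352. The standard error of the arm difference is SD × √(2 × 0.1352/20) = 0.1163 × SD. The stated 0.80 cannot be checked without an SD. Solving for the SD that gives 0.80 yields 2.15 by the normal approximation and 2.09 on t with 38 df. With 38 df, an SD of 1.8 gives power 0.90 and an SD of 2.3 gives 0.72. SD 2.09 is used below, so that the starting point is the plan's 0.80.

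**Step 2: the true variance once block is balanced out.** This is 0.113(1 − b) + 0.887/40:
- b = 0: 0.1352
- b = 0.10: 0.1239
- b = 0.20: 0.1126

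**Step 3: the variance that a no-block analysis estimates.** Each arm has 20 clinics, five from each of four blocks. On average, the within-arm sample variance picks up 15/19 of the block variance 0.113b:
- b = 0.10: 0.1239 + 0.0113 × 15/19 = 0.1328. Standard error too large by √(0.1328/0.1239) = 1.035, about 3.5%.
- b = 0.20: 0.1126 + 0.0226 × 15/19 = 0.1304. Standard error too large by √(0.1304/0.1126) = 1.076, about 7.6%.

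**Step 4: power and type I error.** Simulation of clinic means (100,000 trials per setting, normal random block effects, equal clinic sizes). The test without block uses 38 df and the test with block uses 35 df.

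| Block share b | Power, no block term | Power, block term | Type I error, no block term | Type I error, block term |
|---|---|---|---|---|
| 0% | 0.80 | 0.80 | 0.050 | 0.050 |
| 10% | 0.815 | 0.83 | 0.043 | 0.050 |
| 20% | 0.83 | 0.87 | 0.037 | 0.050 |

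The non-central t calculation for the adjusted test agrees: 0.798, 0.831 and 0.865. At b = 0 the adjusted power is 0.798 against 0.800, so the price of the 3 df is about 0.2 points. With 60 patients per clinic and the SD again set to give 0.80, the results are nearly the same: type I error without block is about 0.036 at b = 20%.

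**Step 5: the timing wording.** Data collection applies a facilitation-start anchor to all 40 clinics. Outcomes dates the second survey at the end of the 12-month intervention and the third a year later, again with no control anchor. The Abstract gives 12 and 24 months without a time zero. If the block's start date is meant for both arms, the two arms align and nothing is wrong, but no sentence says so.

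**The case against.** **The model statement may be incomplete.** The article names nesting levels, not a covariate list, and stratification terms are often left to a full protocol or SAP that is not shown. This stands in part. It cannot be said that the trial will ignore block, only that the model as written does.

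**Omitting block biases nothing.** Correct. With 5:5 balance, the difference in clinic means is the same with or without the term. A reader might infer a biased estimate or an inflated false-positive rate. The design points the other way: the error is conservative.

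**The gain is easy to overstate.** A reader might compare 0.83 or 0.87 with the plan's 0.80. That comparator is wrong. If blocks explain variance, the true variance is smaller and the unadjusted test gains power too. The difference due to the block term is about 2 points at a 10% share and about 4 at 20%.

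**The block share is assumed, and the model studies change.** Both parts stand. Nothing shows that clinics in one network, started over nine months, differ by wave. If the arm effect is tested as a difference in within-clinic change, stable block differences largely cancel. The shares above should then be read as shares of the between-clinic variance in the tested quantity.

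**The control clock is not wrong.** One could read the visit sentence as starting a control clinic's clock at its delayed facilitation, so that its 12-month visit follows a year of intervention. The documents do not support this. The sentence refers to the initial intervention, which the protocol keeps apart from the delayed one, and control practices are facilitated only after serving as controls. The sentence also governs site visits, that is, the surveys and cost data. A1c comes from dated chart entries that can be aligned to any index date. What remains is an undefined anchor.

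**Conclusion.** The point holds in limited form. Randomisation is restricted by calendar block and the stated model does not reflect it. Fitted as written, it gives an unbiased arm estimate with a standard error that is too large whenever blocks differ. For assumed block shares of 0 to 20%, the loss is about 0 to 4 points of power, and type I error runs from 0.050 down to about 0.037. These figures rest on an implied SD of 2.09, equal clinic sizes, 5:5 balance and an assumed block variance. The documents fix only the ICC, the effect, the numbers of clinics and patients, and the target power.

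The change is worth making because it is cheap and follows the randomisation already chosen, not because validity is threatened. The timing matter is a clarification that would not carry a point alone. The documents do not show a comparison that is non-concurrent or contaminated by delayed facilitation.

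**What to change.** 1. In the models for Aims 1 to 3, add randomisation block as a fixed effect alongside the clinic and patient levels. Cost: one sentence and 3 df, or about 0.2 points of power if blocks explain nothing.
2. Block-by-time terms are optional. They are relevant mainly if the arm effect is tested as a difference in change and trends may differ by wave. They bring the total to 6 df if time enters as a single contrast.
3. State that time zero for all ten clinics in a block, intervention and control, is that block's start date. Use it for the 12- and 24-month survey visits and for the 12-month cut of the chart data.
4. Reconcile that definition with the timing of the delayed intervention, so that the text shows how the control clinics' 12-month assessment and the start of their facilitation are ordered.

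Items 3 and 4 cost wording only.

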### Data collection

To obtain the dependent and independent variable necessary to accomplish specific aims one through three, clinician and staff surveys will be administered and medical record abstracted in each clinic. Site visits will be conducted in all 40 clinics and will be conducted three times: at baseline after enrollment but prior to randomization, and 12 and 24 months after starting the initial facilitation intervention in each clinic. During each site visit, clinicians and staff will complete surveys to measure the presence of the elements of the CCM as well as communication among clinicians and staff (see description of outcomes below).

The second method of data collection is a blinded medical record abstraction for the primary outcomes: A1c, BP, and lipid levels. This will be accomplished by a trained chart auditor who is blinded to assignment of clinics to intervention or control groups. The abstraction will take place at baseline, after the conclusion of the delayed intervention in the control clinics and 12 months after the end of the intervention in the initial intervention clinics.

For the fourth specific aim, a project accounting system will be developed to allocate all project expenses to a set of cost categories (cost pools) to assess the cost from the perspective of the organization conducting the intervention. Definitions and rules for assigning expenses into cost pools will be developed by the PI and project director in the first three months of the project. The second goal of specific aim four is to estimate the direct variable cost of conducting PF in the typical primary care facility. Net cost to the practice of implementing the intervention is: Revenues – (service cost plus cost resulting from intervention). Revenue will be tracked from billing data downloaded from each practice during each of the three site visits to track utilization and charges for all patients with type 2 diabetes in each practice for the 12 months prior to intervention, and at the end of 12 month period following the first facilitation visit. The methods used to collect cost data include meeting with the office manager at each practice during each site visit, and the collection of detailed field notes by the facilitators during direct observation in each practice. These data will be used to estimate the fixed and incremental cost of all resources used by the practice to implement the new strategy. We anticipate that these new resources will vary from practice to practice depending on the number of strategies implemented by the practice as a result of the intervention.

### Outcomes

Patient-level outcomes will be measured by collecting data on a random sample of medical records on 60 patients within each clinic at the conclusion of the delayed intervention. All dates and values of A1c, BP, and lipids for the prior 12 months will be collected at baseline and for the intervening time period during the final chart abstraction, for a total of 36 months of values. The random sample of medical records of patients with type 2 diabetes will be selected from a list of all patients with type 2 diabetes seen within each clinic over the prior 12 months generated from each practice's billing system.

Practice-level outcomes will be measured by physician and staff surveys administered three times: at baseline, at the conclusion of the 12-month intervention, and 12 months later. The extent to which the care delivered in each clinic is consistent with the elements of the CCM will be measured with the Assessment of Chronic Illness Care survey (ACIC) [27]. The ACIC measures the presence of the six elements of the CCM. Each item is scored on a 0 to 11 scale and provides sub-scale scores for each of the six CCM components as well as a total score. The validity of the instrument is supported by the findings of a study of an intervention for diabetes and congestive heart failure: all six sub-scales were responsive to process of care improvement [27].

Communication among staff and clinicians will be measured with a survey developed by Shortell and colleagues that was previously validated in health care settings [28]. This instrument captures three aspects of organizational communication: openness [29], timeliness [28] and accuracy [30]. These aspects as measured by this specific instrument have been shown to influence the ability or willingness of health care workers to develop relationships that increase the number and quality of interconnections and information flow, contributing to better self-organization and outcomes [20].

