### Baseline practice assessment

Prior to the first practice team meeting, the facilitators will conduct a one-week detailed assessment in each of the 20 intervention practices [31-33]. This data will be used to prepare an initial practice report that will be used in the first step of the intervention. The data from the assessment will be used to locate potential change points for improving practice change capacity and diabetes service delivery.

The primary data of the assessment will be dictated field notes from observations of the practice environment and clinical encounters. A detailed template will be used as a reminder to the facilitator of topics to be included in the field notes. Observational field notes [34] will be supplemented with collection and review of existing practice documents, including medical charts, flow sheets, patient schedules, personnel lists, mission statements, office protocols, and annual reports. Key informant interviews will be conducted to develop a more detailed understanding of clinician, staff, and patient perception of their goals and performance [35]. Separately, the facilitator will gather data using a standardized medical record review form to obtain performance data on risk factor control (A1c, BP and Lipids) for 60 patients with diabetes in each clinic (see outcomes below). Clinician and staff survey data collected during the initial site visit (see outcomes below), as well as practice characteristics will also be incorporated into the assessment. All qualitative data will be recorded, transcribed, and entered into a text management software program, and an in-depth analyses will be done to guide the subsequent facilitation intervention.

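### The protocol contradicts itself on when the 60 patients per clinic are identified, and one reading lets them be selected after randomisation

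*Protocol article*

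**What the plan says.** **Outcomes.** Patient-level outcomes come from "collecting data on a random sample of medical records on 60 patients within each clinic at the conclusion of the delayed intervention". The charts are "selected from a list of all patients with type 2 diabetes seen within each clinic over the prior 12 months", taken from each practice's billing system; the date from which those 12 months count back is not given. Between these two statements, the section says that values covering the preceding year "will be collected at baseline and for the intervening time period during the final chart abstraction, for a total of 36 months of values".

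**Data collection.** "The abstraction will take place at baseline, after the conclusion of the delayed intervention in the control clinics". In the initial intervention clinics, the later abstraction falls a year after facilitation ends. The abstractor is a trained auditor blinded to assignment. The site visits, which carry the surveys, start "at baseline after enrollment but prior to randomization"; that timing is not stated for the chart sample.

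**Study setting and subjects.** To be eligible, "the practice must have seen at least 60 patients with type 2 diabetes in the past year", and the stated reason is to secure the sample of 60.

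**Baseline practice assessment.** In the 20 intervention practices, "the facilitator will gather data using a standardized medical record review form to obtain performance data on risk factor control". This review is done "for 60 patients with diabetes in each clinic", with a cross-reference to the outcomes.

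**Abstract, and Sample size and analysis.** The primary hypotheses use 12-month data. The model takes repeated measures within patients and patients within clinics.

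**The concern.** The date on which patients are identified decides whether randomisation protects the comparison. If the list is drawn at the end, a patient enters the 12-month A1c analysis only by being diagnosed, coded and still attending after allocation. Patients who died, left or were not seen in the second year drop out, although they may have had a 12-month value. Patients who joined after randomisation enter without a baseline value.

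The toolbox (registry, reminders, group visits, patient activation) can plausibly change who is identified and recalled. Blinding the abstractor does not address this, because the selection happens in the billing list. A random draw from an affected list, or a hierarchical model fitted to it, does not restore comparability either.

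A second uncertainty sits beside the first. The facilitator also reviews 60 charts per clinic for the same risk factors, in intervention practices only, and the text points to the outcomes section. It is not plain that this review is separate from the baseline outcome data.

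**Working it through.** **1. Timeline.** The protocol counts 36 months of values, 12 of them before baseline, so follow-up is 36 - 12 = 24 months. A list drawn at the end and looking back 12 months covers about months 12-24. In that window the control clinics receive the delayed intervention and the initial intervention clinics are past theirs.

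**2. Three readings set against the text.**

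| Statement | A: one cohort from baseline | B: one draw at the end, charts read backwards | C: a new draw at each abstraction |
|---|---|---|---|
| Sample placed at the end of the delayed intervention | fits only if this means collecting, not choosing | fits | fits the final draw |
| Values collected at baseline | fits | conflicts | fits |
| 36 months of values | fits | fits | only by adding different patients' spans |
| Repeated measures within patient | fits | fits | weak: no patient need have both periods |
| Eligibility count of 60 tied to the sample size | fits | indirect | indirect |

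A has the best support, but it needs a strained reading of the sentence that dates the sample. B and C both admit selection after randomisation. No sentence rules them out by saying when the list is drawn or that the same patients are abstracted each time.

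**3. The plan's own power figure.** Inputs from Sample size and analysis: 20 clinics per arm, 40 patients per clinic, ICC 0.113, effect 0.7, power 0.80, alpha 0.05 (two-sided assumed). No A1c standard deviation is given, so the 0.80 cannot be reproduced, only solved backwards.

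- Design effect: 1 + 39 x 0.113 = 5.407.
- Effective n per arm: 800 / 5.407 = 148.0.
- Standard error implied by the stated power: 0.7 / (1.960 + 0.842) = 0.250.
- Implied SD: about 2.15. Check: sqrt(2 x 2.15^2 x 5.407 / 800) = 0.250.

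This gives a yardstick only. It neither supports nor refutes the concern.

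**4. Illustration of selection under a late draw.** Bias = f x g, where f is the excess share of one arm's sample present only because of altered attendance or coding, and g is the A1c gap between those patients and the rest. Both are assumptions; the document gives neither.

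| f | g | Bias | Share of 0.7 | Bias / SE | Two-sided rejection with no true effect | Power at a true 0.7 if the bias opposes it |
|---|---|---|---|---|---|---|
| 10% | 1.0 | 0.10 | 14% | 0.4 | 6.9% | 0.67 |
| 20% | 1.0 | 0.20 | 29% | 0.8 | 12.6% | 0.52 |

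Rejection is 1 - Φ(1.960 - b/SE) + Φ(-1.960 - b/SE), and power is Φ((0.7 - b)/SE - 1.960). Widening the assumptions to f of 10-30% and g of 0.5-1.5 gives a bias of 0.05-0.45 and rejection of 5.5-44%. That spread shows how little the document constrains the size.

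**The case against.** The strongest reply is that a baseline cohort was intended. The Outcomes section speaks of collecting data on a sample at the end, not of first choosing it then. Its next sentence describes charts opened at baseline and extended later. The eligibility criterion ties the 60 to a list available at enrolment, and the Abstract has data on 60 patients per clinic at baseline, 12 and 24 months. This stands as the better-supported reading. It does not remove the contradiction. The repeated-measures model and the 36-month span do not separate a baseline cohort from charts read backwards, so the main textual obstacle to a late draw is the collection at baseline.

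A reader might infer the stronger claim that the sample is certainly drawn late and the primary comparison therefore biased by facilitation. The document does not support that. The late draw is not settled. Even under it, control clinics have had a similar, refined facilitation before the list is drawn, so a net excess in the intervention arm is not shown. The arms would still differ in when they were facilitated, so the lists need not be comparable, but the direction is unknown.

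A reader might also infer that the unblinded facilitator supplies baseline outcomes in the intervention arm. That is mostly answered: the assessment data are said to serve the practice report, and the Data collection section gives baseline abstraction to the blinded auditor. What remains is the loose cross-reference, together with a Design section that mentions blinding only for the final abstraction.

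**Conclusion.** The point holds as a contradiction about when patients are identified, with a real risk attached to one way of following it. The reference date of the 12-month window and the identity of the patients across abstractions are both unfixed. A team acting on the sentence that dates the sample would select patients after randomisation, and no later analysis could reliably undo that.

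The size of any bias is unknown, as is its direction. The 0.10-0.20 points rest wholly on an assumed 10-20% excess and an assumed 1.0-point gap, and amount to less than one standard error. That standard error rests in turn on an SD solved from the stated power. The figures show why the wording should be settled before lists are drawn; they do not show that bias is present.

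**What to change.** **In Outcomes**, state that the 60 patients are drawn once, before randomisation, in all 40 clinics, from the billing list of patients seen in the 12 months before baseline. State that the list is saved and that the same patients are followed for all 36 months whether or not they are seen later. Reword the sentence that dates the sample so that it refers only to the final collection of values.

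**In Baseline practice assessment, Data collection and Design**, reconcile the cross-reference and the blinding statements. The facilitator's chart review feeds the practice report only, and the blinded auditor supplies baseline and follow-up outcome values in both arms.

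**Cost.** The change needs protocol wording and a stored list. Practices must already be able to identify these patients from billing records, and a pre-randomisation visit is planned in every clinic. If a baseline cohort was always intended, only the wording changes.

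**Downside.** Some cohort members will have no later A1c value, so fewer than 60 per clinic may be evaluable at 12 months. The power calculation uses 40 per clinic, so on numbers alone 60 - 40 = 20 could be lost before falling below it. At the back-solved SD of 2.15, power is 0.821 with 60 and 0.800 with 40. A closed cohort does not prevent missing values, but it makes them countable by arm.
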